#### Mesopic microperimetry

Mesopic microperimetry using the MAIA (Macular Integrity Assessment; Centervue SpA, Padova, Italy) assesses central visual function, whilst using fundus-tracking technology to improve test accuracy and reliability [18]. This is a highly useful test as it produces a central threshold sensitivity map with clear and easy to interpret results indicating visual function capabilities. We have shown that microperimetry is a useful, repeatable clinical marker in other inherited retinal diseases [19, 20]. Microperimetry was a main outcome measure in the phase I/II gene therapy clinical trials for *RPGR*-associated RP [21]. Application and utility assessment are still required in other RP subtypes due to the disease’s heterogeneity. Mesopic microperimetry will be used as a marker to identify disease severity and to compare with the other visual function results.

Microperimetry will be performed on all participants completing part one, in a darkened room (light level < 1.0lx), without any formal dark adaptation or any pharmacological pupil dilation [22, 23]. The standard 10−2 test grid (Fig. 3A) will be used, with 4−2 bracketing threshold strategy. Examination involves the presentation of Goldmann size III stimuli of various intensities (0-318cd/m^2^), presented for 200ms, on to a mesopic background (1.27cd/m^2^). The overall dynamic testing range is 0-36dB. A 1-degree diameter red circle will be used as a central fixation target. Prior to testing, subjects will be told about the test and what they are required to do. The right eye is to be tested first followed by the left eye as per clinical convention. The non-tested eye must be occluded throughout.

**Fig. 3 Fig3:**
[figure not shown]
**A**, represents results from the 10-2 rectilinear testing grid used in mesopic microperimetry. **B** and **C** represent results from the radial 37 stimuli testing grid used in scotopic cyan and scotopic red microperimetry testing, respectively

### Part two

#### Scotopic Microperimetry

Scotopic microperimetry is a modified version of microperimetry, that is performed at much lower light levels, using two-colour perimetry to target a spatial assessment of rod and cone photoreceptor scotopic function [24]. For clinical trials, this test could be incredibly useful in identifying rod or cone specific photoreceptors responding to treatments. However, this test can be more difficult for patients to complete, it is prone to ceiling and floor effects [18]. Clinical utility assessment of scotopic microperimetry in patients with RP at different disease stages is vital to enable us to understand whether it is likely to be a practical and appropriate measure.

Scotopic microperimetry testing, will be performed on the S-MAIA microperimeter. Each participant must complete 20 minutes of dark adaptation (light level < 1.0lx) prior to testing [25]. The 37-point scotopic wide radial grid will be used (Fig. 3B), with a 4−2 bracketing threshold staircase strategy and Goldmann size III (0.43degrees) stimulus. Cyan stimuli testing (505nm) is performed first followed by red stimuli (627nm) testing. A 1-degree circular red fixation target (645nm) is used, if this is not seen at the minimum brightness, the luminance will be increased until the fixation target is detected. No formal break will be given between each test. A subset of patient and healthy control participants (at least 50%) will undergo repeat testing on one eye only for repeatability analyses.

#### Qualitative data collection

Patient participants who complete both study parts one and two will be invited to take part in a recorded semi-structured interview, ideally within a few days of completing the study. The aim is to assess participants thoughts and feelings around the practicalities of the different visual function tests being undertaken, as well as suggestions for improving the experience in the future. Interviews will take place over Teams at a mutually agreed time, it is estimated each interview will take around 30–45 minutes. The audio recordings from the interviews will be transcribed and used for thematic analysis.

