### Study procedures

Informed consent will be obtained, in person, by the investigator (appointed research optometrist) prior to completing any study procedures. This is a single visit study that has been carefully designed to fit in and around the NHS outpatient appointments at Oxford Eye Hospital, to minimise the need for participants to return to the eye hospital to take part in the study on a separate day. This is important as the specialist retinal genetic clinics are part of a tertiary referral centre, meaning that patients travel from all over the country to attend. The study has been planned to be as flexible as possible to work around time and room availability constraints, therefore not all the study tests are required to be completed. The study is divided into two parts, part one and part two (Fig. 1). Participants must complete all tests in a single part, although where possible participants will be invited to complete the entire study. A subset of patient participants will be invited to take part in semi-structured qualitative virtual interviews upon completion of the study. Estimated study duration is one hour for each part, two hours in total for the entire study.

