#### Safety

The VFIRD study is observational, there are no therapeutic interventions administered. All visual function tests used in the study are already CE approved and commercially available tests. All assessments are non-invasive and not associated with any serious adverse events. Some participants may find some of the testing tiring, but this has been carefully considered and protocols tailored to minimize fatigue. For patient participants, if any concerns arise during the study, these will be recorded in the patient’s hospital notes and bought to the attention of the patient’s consultant who is responsible for their care. For healthy participants, if any concerns arise regarding reduced visual function, the participants will be advised to see their optometrist or general practitioner for further investigation. Participants may withdraw at any point during the study.

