#### Qualitative sample size

We estimate a sample size of 20–25 participants, although this is flexible. The sample size will be adjusted as deemed sufficient upon ongoing data analyses to ensure data adequacy [29]. These participants will be purposely sampled following completion of the study visual function tests. The participants will all have confirmed inherited eye disease causing similar types of sight loss (loss of night vision and peripheral vision), with variable severity.

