#### Qualitative data analysis

All recorded qualitative semi-structured interviews will be transcribed manually by an approved transcriber. Thematic analysis using Nvivo software will be applied to identify common themes in data regarding participants experiences and feelings of the overall study and specific study tests. These will be summarised using network diagrams to illustrate interpretation. The aim is to explore the accessibility, practicality and acceptability of the different tests [32].

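### Interview invitations go to patients who complete both parts, so interview findings on acceptability and burden miss those who declined or stopped a part because of burden or difficulty

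*Protocol article*

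**What the plan says.** The invitation rule is in Qualitative data collection: "Patient participants who complete both study parts one and two will be invited to take part in a recorded semi-structured interview". Two other sections fit with it. Study procedures says "A subset of patient participants will be invited to take part in semi-structured qualitative virtual interviews upon completion of the study", and Qualitative sample size says "These participants will be purposely sampled following completion of the study visual function tests". The target there is 20–25 interviews, described as flexible, with patients covering a range of severity.

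On purpose, Study outcomes lists patients' experience of the tests with the secondary outcomes, including whether the tests are acceptable and whether they need changing. Qualitative data analysis states: "The aim is to explore the accessibility, practicality and acceptability of the different tests". The clinical utility model under Assessment of clinical utility & statistical methods includes patient burden in its definition of acceptability.

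On completion, Study procedures says "Participants must complete all tests in a single part, although where possible participants will be invited to complete the entire study", and explains by reference to limited time and rooms that "not all the study tests are required to be completed". Safety acknowledges that some participants may find testing tiring and adds: "Participants may withdraw at any point during the study".

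**The concern.** Entry to the interview depends on having finished the full battery, estimated at two hours. Finishing is closely tied to what the interview is meant to assess, namely how burdensome and acceptable the tests are. A patient who declined part two, or stopped during it, because it was too tiring or too hard is well placed to say what would need to change. The article gives that patient no route to an interview.

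At stake is the interview evidence on acceptability and burden, and within it chiefly the evidence on scotopic microperimetry. That test makes up part two, and the article says its utility at different disease stages has to be established before anyone can tell whether it is practical. If the views collected come only from those who got through it, the study could report it as more acceptable than patients in general would find it, and a future trial could adopt it on that basis.

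**Working it through.** The article states no figure on this point that could be reproduced. The check sets the rules beside the aims.

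1. **Who can be interviewed.** Qualitative data collection names patients who complete both parts. The phrases about timing in Study procedures and Qualitative sample size are compatible with this. Read alone, they could also cover someone who has finished a single part, but neither section says so, and no section offers an interview to a patient who did one part or stopped during a test. The sentence does not contain the word *only*, but it is the one explicit statement of who is invited.

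2. **Who is in the study.** Completing one part is sufficient, and both parts are done where possible. The article therefore expects some of the 40 patients not to complete both.

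3. **Why a patient might not complete both.** The article supports two kinds of reason. One is logistic: time and room limits, in a study fitted around clinics to which patients travel from across the country. The other is burden or difficulty: testing may be tiring (Safety), and scotopic microperimetry is harder to complete (Scotopic Microperimetry). Patients left out for the first reason need not differ in their views of the tests. Those left out for the second would be expected to be less favourable, so their absence tends to favour the tests.

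4. **Whether another provision makes up for it.**
   - Purposive sampling across severity acts among the patients whom the invitation rule admits. It cannot bring in anyone else.
   - The statistical methods count how many participants manage each test, show the distribution of results and record test time. The counts cover practicality and would reveal failures on scotopic microperimetry. They do not record reasons, views or suggestions, so they do not replace interviews on acceptability and burden.
   - Reaching 20–25 interviews would not expose the gap, because all of them can come from completers if enough patients complete.

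5. **Size.** Under the stated rule, the number of non-completers interviewed is zero, however many there are. The resulting bias cannot be computed. It depends on the share of patients who do not complete both parts and on how many of them stop for burden rather than logistics, and the article gives neither. If nearly all one-part participation is logistic, the bias is small. If much of it reflects burden, the interview findings on part two lose the patients with most to say about it.

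**The case against.** The rule has a sensible rationale. The interviews concern the different tests, and a patient who has taken the acuity, mesopic and scotopic tests can compare them, whereas a one-part patient cannot. In a small purposive sample, asking for experience of the whole battery is defensible. This stands as a reason for interviewing mostly completers. It does not require interviewing completers alone.

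Single-part participation is also, by the article's own account, a scheduling matter. This stands too: nothing shows that non-completers are mainly dissatisfied, so no size can be put on the bias.

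A reader might infer three stronger things that the article does not support.

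- *That everyone who found the tests unacceptable is shut out.* The rule selects on completion, not opinion. A patient who disliked the tests but finished both parts can be interviewed, and the interviews ask for suggested improvements. Nor does the article equate a poor scotopic result with non-completion, so a patient at the floor of the scale may still have completed part two.
- *That practicality is judged on completers only.* The completion counts address it separately.
- *That the interview target is in jeopardy.* The 20–25 is flexible and is adjusted for data adequacy, and with no completion rate given no shortfall can be shown.

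**Conclusion.** The concern holds in a limited form. As written, the invitation rule leaves out of the interviews any patient who declined or stopped a part because of burden or difficulty. The interview findings on acceptability and burden, above all for scotopic microperimetry, therefore tend to favour the tests.

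The direction rests on one assumption: that patients who stop for burden or difficulty view the tests less favourably than those who finish. The size is unknown and could be small. The point touches one qualitative secondary outcome and leaves the quantitative comparisons and the completion counts as they are. It is worth correcting because the selection is on a variable tied to what the interviews assess, and the correction is cheap.

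**What to change.** In Qualitative data collection, replace the invitation rule with wording such as: *Patient participants who attempted at least one part will be invited to interview, including those who completed one part only or stopped a test early. Patients who have withdrawn from the study will be approached only if their consent covers further contact.*

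In Qualitative sample size, keep the flexible 20–25, drawn mostly from completers. Add completion status (both parts, one part, stopped early) as a purposive-sampling criterion beside severity, with a few places held for non-completers. Bring the related sentence in Study procedures into line.

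On the study worksheets, record the reason for each non-completion, separating logistics from burden or difficulty. This would also show how far the concern matters in practice.

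The cost is a protocol amendment and one extra item on the worksheets. The number of interviews and the testing do not change. The downside is that one-part patients can comment only on the tests they took, so a few interviews will not support comparison across the whole battery. The limit on approaching withdrawn patients means that some of those most affected by burden may still not be heard.

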#### Additional data

Demographic data including age and ophthalmic history from the patient participants’ hospital notes will be collected as part of the study. Structural outcome measures obtained from retinal imaging includes optical coherence tomography (OCT) and fundus autofluorescence attained using the Heidelberg Eye Explorer software (Heidelberg Engineering, Heidelberg, Germany) will be used to investigate structure-function correlations. Structural outcome measures provide objective assessments by combining structural dimensions to functional endpoints, which can improve predictive accuracy for short-term data, increase the statistical power of tests, potentially resulting in smaller sample sizes being sufficient [7, 26]. However, structural endpoints require evidence of strong correlations with functional biomarkers to be accepted as clinical trial endpoints [7, 13].

#### Safety

The VFIRD study is observational, there are no therapeutic interventions administered. All visual function tests used in the study are already CE approved and commercially available tests. All assessments are non-invasive and not associated with any serious adverse events. Some participants may find some of the testing tiring, but this has been carefully considered and protocols tailored to minimize fatigue. For patient participants, if any concerns arise during the study, these will be recorded in the patient’s hospital notes and bought to the attention of the patient’s consultant who is responsible for their care. For healthy participants, if any concerns arise regarding reduced visual function, the participants will be advised to see their optometrist or general practitioner for further investigation. Participants may withdraw at any point during the study.

### Statistical analysis

#### Study sample size

There is insufficient data on the variance of most of these visual function tests, since many have not been used in patients with inherited retinal disease and more specifically, rod-cone degeneration, to enable accurate method comparison and power calculations. The data obtained from this study will be used to estimate power and calculate sample sizes in future clinical trials. Therefore, we apply a pragmatic sample size estimation. On average 30 patients a week attend the eye hospital with inherited retinal disease.

Around 40% of patients with inherited retinal disease have RP [27]. From this we calculate 12 patients with RP attend the eye hospital per week on average. Not all will be eligible. Those with advanced disease resulting in unmeasurable vision will be excluded. We estimate 50% will be eligible. Patients are referred to our tertiary referral centre to learn more about their condition and enquire about research. From previous studies, patient recruitment rate has been good, with at least four in five patients willing to take part in research studies. We estimate there will be four eligible patient participants willing to take part each week. The project must work around other research and clinic availability.

We have allocated 15 months (65 weeks) for data collection. To avoid patient and participant inconvenience and clinic disruption, it will not be possible to test more than two participants in one day. Some weeks we will be able to complete testing for two participants (particularly if they are together), while other weeks it may be only possible to complete one. Therefore, we have set a conservative target of 1–2 participants per week. From this we generated an estimated sample size of 40 patient participants and 40 healthy volunteer participants. We believe 80 participants is achievable and will provide sufficient end-to-end data distribution for this early-stage study. Our work investigating tests in other eye disease have used similar sample sizes [19, 28].

#### Qualitative sample size

We estimate a sample size of 20–25 participants, although this is flexible. The sample size will be adjusted as deemed sufficient upon ongoing data analyses to ensure data adequacy [29]. These participants will be purposely sampled following completion of the study visual function tests. The participants will all have confirmed inherited eye disease causing similar types of sight loss (loss of night vision and peripheral vision), with variable severity.

#### Assessment of clinical utility & statistical methods

Smart’s clinical utility multi-dimensional model will be used to comprehensively explore the clinical effectiveness but also evaluate the tests ease and efficiency of use, their relevance and more importantly patient’s and participant’s perspectives [30]. The model is broken down into four aspects but there is some overlap between these:

Appropriateness – are the tests effective and relevant?Accessibility – are they readily available and affordable?Practically – are they functional and straightforward?Acceptability – are they ethical and of acceptable patient burden?

To assess appropriateness and practicality of these new assessments we will apply descriptive statistics to indicate the number of participants able to complete each test. Followed by distribution plots and frequencies to indicate the spread of data. An appropriate visual function test is one that shows a large range of results across the disease spectrum with limited ceiling and floor effects. It should distinguish between healthy controls and patient participant’s vision. To investigate this, comparative statistics will be applied. The degree of difference will be analysed using Cohen’s D to calculate the effect size. ANOVA or non-parametric equivalents will be used to test for statistically significant differences, between patients and controls. The threshold of statistical significance will be set at p < 0.05. Test time will be measured and used as a quantitative marker for accessibility.

To investigate test-retest variability, a subset of participants will complete the study tests to enable Bland-Altman repeatability analyses with resulting limits of agreement and coefficient of repeatability indices. This will identify a clinically significant criterion [31]. Patient participants may be categorised by their genotype and their clinical characteristics, to develop greater understanding of genotype-phenotype correlations.

Regression analyses will be applied to compare the new visual function test results to currently used measures including VA, patient reported outcome measure questionnaires and ocular imaging structural analyses. A strong correlation would suggest tests are assessing similar aspects of the patient’s vision. This is important since it can help us understand which visual function assessments may be more relevant to specific patient reported experiences. Missing or incomplete data will be excluded from analyses.

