## Methods

The VFIRD study is a cross-sectional prospective study involving two groups of participants: participants with an inherited retinal disease causing a rod-cone degeneration (n = 40), and age and gender matched healthy controls (n = 40). Healthy controls will be recruited from members of the general public through advertisements or from individuals accompanying patients (must be non-blood relatives) to eye hospital appointments. Patient participants will be recruited from the NHS specialist ocular genetics clinic at Oxford Eye Hospital. This publication refers to protocol version 2.1 dated 22/11/2022 and was developed using the STROBE and SPIRIT reporting guidelines where applicable [15, 16]. The study is sponsored by the University of Oxford. A patient and public involvement (PPI) group was set up with representatives providing feedback which supported the study design. Ethics approval has been obtained from the NHS Health Research Authority Black Country Research Ethics Committee (reference 20/WM/0283).

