**Exclusion criteria**
**The patient may not enter the study if ANY of the following apply**:
• Pre-existing amblyopia or squint would exclude that eye, but the unaffected eye would still be eligible
• History of eye problems, eye treatment or eye surgery other than refractive error. If an eye problem exists in one eye, the fellow eye is still eligible
• Been involved in an interventional research trial where they have received a treatment for their eye condition

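### The patient-control comparison is fixed as plain ANOVA, which uses neither the age and gender matching nor any allowance for two correlated eyes per person

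*Protocol article*

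**What the plan says.** The section on clinical utility and statistical methods fixes the group comparison: "ANOVA or non-parametric equivalents will be used to test for statistically significant differences, between patients and controls". It adds that "The degree of difference will be analysed using Cohen’s D to calculate the effect size" and that "The threshold of statistical significance will be set at p < 0.05". For relations between tests, "Regression analyses will be applied to compare the new visual function test results to currently used measures including VA", and also to questionnaires and imaging. It names no covariate, pair or participant term, and does not say whether the unit is the eye or the person. Incomplete data are left out.

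The design sections describe data with more structure:

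- Methods: the 40 controls are "age and gender matched healthy controls", found through advertisements or among unrelated companions of patients. Whether matching is individual or by frequency is not stated.
- Table 2: low-luminance, standard and Moorfields chart acuity are each measured in the right eye, the left eye and binocularly.
- Mesopic microperimetry: "The right eye is to be tested first followed by the left eye as per clinical convention".
- Table 1, exclusion criteria for patients, with the same rule for controls: "If an eye problem exists in one eye, the fellow eye is still eligible". A participant can therefore contribute one eye or two.
- Study procedures: a participant may complete only one of the two parts.

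**The concern.** An analysis should use the structure that the design creates. Two features are at issue.

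**Matching.** Age and gender are balanced by design because they are expected to matter. A comparison that then ignores them leaves the variance they explain in the error term. Matching of the 40 and 40 at recruitment also does not guarantee balance test by test: people may do only one part, and incomplete data are dropped, so the set analysed for a given test can differ from the matched set. Nothing in the stated comparison corrects for that.

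**Two eyes.** Fellow eyes of one person are correlated. ANOVA, its usual rank equivalents and ordinary regression assume independent observations. If both eyes enter as separate observations, precision is overstated. Against a questionnaire score, which exists once per person, an eye-level regression would also count each score twice.

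Separation of patients from controls is one of the article's criteria for an appropriate test, and the sample size section says that the data will feed power and sample size calculations for later trials. Misjudged precision would carry forward into those.

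**Working it through.** **The plan's own figure.** The sample size is a feasibility figure: 30 x 0.40 = 12 patients with retinitis pigmentosa per week, x 0.50 = 6 eligible, x 0.80 = 4.8 willing (the article says four). Then 65 weeks at 1-2 participants gives 65-130, and the target of 80 lies in that range. No variance, effect size or power is stated, so the article offers no precision figure to reproduce.

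**Inputs.** From the article: 40 people per group, up to two eyes each (at most 2 x 40 = 80 eyes per group), threshold 0.05. Assumed: a two-sided test, inter-eye correlation ρ, correlation r between matched partners, a standardised difference of 0.6 for the power illustration, and an age R² of 0.20. The article gives none of these.

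**Step 1: both eyes entered as independent.** The true variance of the group difference is (1 + ρ) times the naive one. Effective eyes = 80/(1 + ρ). True type I error = 2 x [1 − Φ(1.96/√(1 + ρ))].

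| ρ (assumed) | effective eyes per group | naive/true SE | true type I error |
|---|---|---|---|
| 0.3 | 62 | 0.877 | 0.086 |
| 0.5 | 53 | 0.816 | 0.110 |
| 0.7 | 47 | 0.767 | 0.133 |
| 0.8 | 44 | 0.745 | 0.144 |
| 0.9 | 42 | 0.725 | 0.155 |

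Simulation (20,000 runs) gave 0.109, 0.136 and 0.154 at ρ = 0.5, 0.7 and 0.9. People with one eligible eye would bring these figures down.

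**Step 2: one value per person.** In the same simulations the type I error was 0.047-0.051 for the mean of two eyes and 0.049-0.053 for one eye, so both are close to nominal.

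**Step 3: matching ignored, one value per person.** The true standard error is √(1 − r) times the one used, so type I error = 2 x [1 − Φ(1.96/√(1 − r))]: 0.039, 0.028 and 0.019 at r = 0.1, 0.2 and 0.3. The test is conservative. At a difference of 0.6 with 40 pairs, power is:

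- r = 0: 0.77 either way
- r = 0.2: 0.79 unpaired, 0.85 paired
- r = 0.3: 0.81 unpaired, 0.89 paired

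In covariate terms, if age explains 20% of within-group variance, adjustment multiplies the standard error by √0.8 = 0.894, a cut of about 11%.

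**Step 4: both together.** The variance ratio is (1 + ρ)(1 − r). At ρ = 0.7 and r = 0.2 it is 1.7 x 0.8 = 1.36, giving 0.093. At ρ = 0.7 and r = 0.4 it is 1.7 x 0.6 = 1.02, giving 0.052.

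**Step 5: regressions among patients.** With both variables at eye level and the same ρ, the variance factor is about 1 + ρ². Simulated type I error for 40 people and 80 eyes was 0.080, 0.108 and 0.151 at ρ = 0.5, 0.7 and 0.9. No matched pair is involved here.

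**The case against.** The strongest reply is that the article never makes the eye the unit of analysis. Its language is about people: it counts participants able to complete each test, compares patients with controls, and sizes the study at 80 participants. Unit of analysis, choice of eye and covariates commonly sit in a full protocol or analysis plan, and this article condenses one. With one value per person, ordinary ANOVA holds its level (step 2).

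Much of this stands, and it rules out several stronger readings:

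- A reader might infer that the planned p-values and intervals are wrong. The article does not support that. The inflation applies only if eyes are pooled without a participant term.
- A reader might infer that the two omissions compound each other. They oppose each other (steps 1 and 3) and can nearly cancel (step 4).
- A reader might extend the matching point to the regressions. Regressions of one test on another among patients have no matched partner to ignore.
- A reader might suppose that repeatability data suffer from two-eye clustering too. Table 2 repeats low-luminance and standard acuity on the right eye only and the Moorfields chart on the left eye only, and the scotopic repeat is on one eye.

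Analysing one eye by a rule set in advance is also valid. Averaging two eyes multiplies the one-eye standard error by √((1 + ρ)/2), a cut of about 13% at ρ = 0.5 and 5% at ρ = 0.8. Pooling would mainly affect the precision of Cohen's d, not its point estimate.

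What the reply does not remove is the mismatch within the article. It fixes the test family and threshold and declares a matched design, and that family as described makes no use of the matching. The per-eye data structure is likewise set out in detail with no rule for handling it in the main comparison.

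**Conclusion.** The concern holds in a limited form. The patient-control comparison as described omits the matching factors. That loses precision to the extent that age and gender predict the outcome, and it leaves imbalance in the test-specific subsets uncorrected. The loss is about 11% of the standard error at an assumed age R² of 0.20, and nil if the factors do not predict the outcome. How much imbalance will arise cannot be known from the article.

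Separately, the article leaves open an eye-level analysis that would be anti-conservative: type I error of about 11% at an assumed inter-eye correlation of 0.5 and 14% at 0.8, with all 80 eyes per group present. This is a conditional risk, not a stated error. It covers group comparisons of monocular acuity and mesopic microperimetry, and eye-level regressions. Group comparisons of binocular acuity and questionnaire scores are person-level and unaffected. The net effect of both features depends on two correlations that the article does not give. The point merits a change of wording and does not undermine the study.

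**What to change.** For the patient-control comparison, replace ANOVA with a linear model containing group, age and gender, or the matched pair if matching is individual, and state which type of matching is used. Where both eyes are analysed, add a participant random effect or cluster-robust standard errors. Take the standardised difference and its interval from that model. If a rank test is kept for a skewed outcome, apply it to one value per person or use a version that allows for clustering.

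For regressions, cluster on participant when both variables are at eye level. When the other variable is a questionnaire score, use one value per person, for example the binocular acuity already scheduled in Table 2. The matching factors are not at issue there.

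The cost is analysis wording only: age is already collected, gender is needed for the matching, and no further testing is required. The downside is that p-values from any eye-level analysis become less favourable than a naive analysis would show.
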